# Efficacy of the nano curcumin supplementation on fibrosis, steatosis, inflammatory and metabolic status of liver fibrosis patients with non-alcoholic fatty liver origin: a study protocol for a double-blind randomized controlled trial

**DOI:** 10.1186/s40795-026-01252-0

**Published:** 2026-02-02

**Keywords:** Dietary supplements, Fibrosis, Random allocation, Clinical trial, Iran

## Abstract

**Background:**

Liver disease related to alcohol consumption and non-alcoholic fatty liver disease (NAFLD) are among the leading causes of liver fibrosis. Curcumin, due to its anti-fibrotic and anti-inflammatory effects, has been proposed as a potential therapeutic agent. However, its clinical application is limited by poor stability, solubility, and bioavailability. Nanocurcumin, a nano-formulated version of curcumin, overcomes these limitations. This study aims to evaluate the efficacy of Nanocurcumin supplementation in improving fibrosis, steatosis, inflammation, and metabolic status in patients with liver fibrosis of NAFLD origin.

**Methods:**

This double-blind, randomized, placebo-controlled trial is being conducted at the Gastroenterology Clinic of Shariati Hospital (Tehran, Iran). Fifty patients aged 30 to 70 years are enrolled and randomly assigned to the intervention or placebo group using a block balanced randomization method. The intervention group receives one capsule of Nanocurcumin (40 mg, twice daily), while the placebo group receives an identical placebo capsule. The primary outcomes include liver fibrosis and steatosis, assessed via FibroScan at baseline and at the end of the study. Secondary outcomes include changes in inflammatory markers, metabolic parameters, liver function tests, anthropometric measures, and blood pressure over the 16-week intervention period.

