Emerging research highlights the potential of curcumin, a polyphenolic compound derived from turmeric, in managing various health conditions. Its therapeutic effects are primarily attributed to its anti-inflammatory, antioxidant, and anti-fibrotic properties. However, curcumin’s clinical application is hindered by its poor bioavailability, rapid metabolism, and low solubility in bodily fluids [21–23]. To overcome these limitations, nanotechnology has been employed to develop Nanocurcumin formulations, which enhance curcumin’s stability, solubility, and bioavailability. Nano carriers such as liposomes, polymer micelles, and solid lipid nanoparticles have shown promise in improving the delivery and efficacy of curcumin in various therapeutic contexts [19, 20].

This study aims to bridge the gap in clinical evidence regarding the efficacy of Nano curcumin in treating liver fibrosis of NAFLD origin. By conducting a randomized controlled trial, we aim to generate data on the therapeutic potential of Nanocurcumin. This evidence will help inform clinical practice and guide the development of effective treatment strategies for liver fibrosis. The primary objective of this study is to evaluate the efficacy of Nanocurcumin supplementation in the treatment and slowing of liver fibrosis and steatosis progression in patients with NAFLD-related fibrosis. Secondary objectives include assessing changes in inflammatory markers, metabolic parameters, liver function tests, anthropometric measures, and blood pressure. The findings from this study will contribute to a better understanding of Nanocurcumin’s role in managing liver fibrosis and may support its potential as a therapeutic option for patients with NAFLD-related fibrosis.

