### Sample size

The sample size is determined based on the study primary outcome (i.e., liver fibrosis). It was calculated using G*Power version 3.1.9.2 using the values from the previous study [30]. Therefore, by considering the effect size of 0.9, type I error (α) of 5% and statistical power (β) of 80%, and an attrition rate of 10%, the total sample size was calculated to be 50 patients, with 25 patients allocated to each of group.

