### Statistical analysis

In this study, data is statistically analyzed using SPSS version 24 software. The Chi-Square test is utilized to compare categorical variables between two groups. Quantitative data will be assessed for normality, and the data with normal distribution will be compared using an independent sample t-test. Alternatively, the Mann-Whitney U test will be employed for non-normally distributed data. For outcome analysis, the ANOVA/ANCOVA will be used. A statistical significance level of *P* < 0.05 will be considered.

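### Fibrosis and steatosis are both named primary, but N = 50 was computed for fibrosis alone and no success rule accompanies the single 5% level, so the stated error and power are secured for fibrosis only

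*Protocol article*

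**What the plan says.** The Protocol article describes the primary outcome in two ways.

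- **Two outcomes.** The Methods part of the abstract says "The primary outcomes include liver fibrosis and steatosis, assessed via FibroScan at baseline and at the end of the study". The primary objective, in the Background, is to evaluate the "efficacy of Nanocurcumin supplementation in the treatment and slowing of liver fibrosis and steatosis progression in patients with NAFLD-related fibrosis". The Primary outcomes section covers both stiffness (kPa) and CAP (dB/m).
- **One outcome.** The Sample size section says "The sample size is determined based on the study primary outcome (i.e., liver fibrosis"), in the singular. It gives one effect size ("by considering the effect size of 0.9"), a 5% type I error, 80% power and 10% attrition, and arrives at 50 patients, 25 per group. No effect size is given for steatosis.

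The Statistical analysis section sets one level: "A statistical significance level of *P* < 0.05 will be considered". It gives no order of testing, no division of alpha and no rule for success on the primary objective.

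**The concern.** How many primary hypotheses there are, and which of them the sample size protects, is settled at protocol level. Here the sections disagree, and an analysis plan written from this text would inherit the conflict.

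The choice of headline result stays open until the data are known. A significant CAP result with null stiffness could be reported as meeting a primary outcome, although the trial was not sized for steatosis and enrols patients by fibrosis stage (F2 or above). The opposite reading, that both outcomes must succeed, carries less power than the reader is told. The 5% and 80% in the Sample size section therefore cannot simply be carried over to the objective in the Background.

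**Working it through.** **Inputs from the Sample size section.** Effect size 0.9, read as a standardised mean difference for fibrosis; alpha 5%; power 80% (printed beside the symbol β, read as power); attrition 10%; 25 per arm. Sidedness is not stated. Two-sided is assumed, because one-sided calculations give totals of only 36 to 38.

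**Step 1: the plan's own figure.**
- Normal approximation: 2 × (1.96 + 0.84)² / 0.9² = 19.4, so 20 per arm; 20 / 0.9 = 22.2, so 23 per arm, 46 in total.
- Exact t test: 21 per arm; 21 / 0.9 = 23.3, so 24 per arm, 48 in total.
- Mann-Whitney (relative efficiency 3/π): 21 × π/3 = 22.0, so 22 per arm; 22 / 0.9 = 24.4, so 25 per arm, 50 in total.

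The stated 50 reproduces for fibrosis.

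**Step 2: power for fibrosis alone.** Completers: 25 × 0.9 = 22.5, taken as 22 per arm. Noncentrality is 0.9 × √(22/2) = 2.985 on 42 degrees of freedom. Power at two-sided 5% is 83.0% (81.2% for Mann-Whitney). The stated 80% is met.

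**Step 3: either outcome suffices, each tested at 5%.** If the two tests are independent, the familywise error is 1 − 0.95² = 9.75%. For correlated tests (bivariate normal) it is 9.5% at correlation 0.3, 9.1% at 0.5 and 8.3% at 0.7; the upper bound is 10%. Power for at least one outcome cannot fall below the 83% for fibrosis. Only the 5% fails.

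**Step 4: both outcomes required, each tested at 5%.** The chance of a false joint claim is at most 5%. With equal effects of 0.9 and independence, power is 0.830 × 0.830 = 69%. Simulation of two correlated t statistics at 22 per arm, with the fibrosis effect at 0.9, gives:

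| Correlation | Steatosis effect 0.9 | 0.7 | 0.5 |
|---|---|---|---|
| 0 | 69% | 52% | 31% |
| 0.3 | 71% | 54% | 33% |
| 0.5 | 73% | 57% | 35% |
| 0.7 | 75% | 59% | 36% |

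The steatosis effects and the correlations are assumptions, because the article gives neither. Under independence, 80% power for both would need 0.80 / 0.830 = 96% power for steatosis, an effect well above 0.9. Only the 80% fails.

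**Step 5: fibrosis first, then steatosis only if fibrosis is significant.** Fibrosis keeps its 5% and its 83%, and the familywise error over the two outcomes stays at or below 5%.

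**Step 6: alpha split equally, 2.5% each.** With 22 per arm, fibrosis power is 74%. Restoring 80% takes 25 completers per arm (exact t); 25 / 0.9 = 27.8, so 28 per arm, 56 in total.

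**The case against.** The strongest reply is that the Sample size section claims 80% power for fibrosis only, and that claim is correct. The error inflation needs an either-outcome rule, which the article nowhere states. Its Discussion speaks of positive effects on fibrosis and steatosis together, which points towards requiring both, and then no inflation arises. The article is also a condensed account: testing order and multiplicity methods commonly sit in an analysis plan, and the Statistical analysis section neither applies nor rules out an adjustment.

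Much of this stands. The inflation is conditional, and the absence of a multiplicity method is not in itself the fault. What remains is a conflict between sections that are shown. Condensing does not turn two primary outcomes into one, and an analysis plan cannot set an order or a split without first deciding which section is right. The Discussion sentence is about follow-on research and is not a decision rule. If it were read as one, it would select the rule under which power falls short.

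A reader might go further and infer that the 5% and the 80% both fail. The documents do not support that: as steps 3 to 5 show, no single rule breaks both. A reader might also extend the point to the secondary outcomes. That is not supported either. They are declared secondary, nominal testing of such outcomes is ordinary, and any multiplicity handling for them belongs in the analysis plan.

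**Conclusion.** The concern holds in conditional form. The article contradicts itself on the number of primary outcomes, and its stated 5% and 80% are secured for fibrosis alone. For the two-outcome objective one of the two figures is not secured: either the familywise error is about 8% to 10% (correlation 0.7 down to 0), or power for both is about 69% to 75% with steatosis at 0.9, and 31% to 59% with steatosis at 0.5 to 0.7. Which applies cannot be settled from the text.

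These figures assume two-sided tests, 22 completers per arm, 0.9 as a standardised difference, and the effects and correlations listed for steatosis. The contradiction between the sections depends on none of these assumptions. The sample size of 50 is not itself in error.

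**What to change.** Name liver stiffness in kPa as the single primary outcome, tested at two-sided 5%, as the Sample size section already assumes. Test CAP next, also at 5%, and treat it as confirmatory only if stiffness is significant. Bring the abstract, the primary objective in the Background, the Primary outcomes section and the Sample size section into line.

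This adds no patients and costs no alpha. The price is that a positive CAP result with null stiffness would no longer be confirmatory. An alpha split (about 56 patients) or co-primary outcomes, with the trial powered for both, would also be valid but would need more patients.

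Timing matters. The article calls the trial ongoing but expected completion by mid-2025, and it was published in February 2026. The change should be dated, recorded in the registry entry and made before unblinding. If the data are already unblinded, the report should disclose the conflict and present both outcomes with their multiplicity stated.

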**Discussion:**

This trial is currently ongoing. Recruitment is expected to be completed by the end of 2024, and the trial is anticipated to be fully completed by mid-2025. If Nanocurcumin supplementation demonstrates positive efficacy, it may serve as a potential therapeutic approach for patients with liver fibrosis.

**Trial registration:**

Iranian Registry of Clinical Trials IRCT20210427051098N2 (Available from: https://irct.behdasht.gov.ir).

Date and version identifier: April 20, 2023; approved version by the IRCT.

**Supplementary Information:**

The online version contains supplementary material available at 10.1186/s40795-026-01252-0.

## Background

Non-alcoholic fatty liver disease (NAFLD) is an increasingly prevalent condition, closely associated with modern lifestyle factors such as poor diet, obesity, and sedentary behavior [1]. It encompasses a spectrum of liver conditions, ranging from simple steatosis (fatty liver) to non-alcoholic steatohepatitis (NASH), which can progress to liver fibrosis, cirrhosis, and ultimately liver failure or hepatocellular carcinoma [2]. The liver’s crucial role in metabolism, detoxification, and immune modulation makes it particularly vulnerable to metabolic imbalances and inflammatory processes inherent in NAFLD [3].

Liver fibrosis is a key factor in the progression of NAFLD to more severe forms. It is characterized by excessive accumulation of extracellular matrix proteins, particularly collagen, leading to scarring and impaired liver function [4]. This process is driven by chronic liver injury and inflammation, which activate hepatic stellate cells (HSCs) to transform into fibrogenic myofibroblasts [5, 6]. Despite the significant global health burden posed by liver fibrosis, current therapeutic options are limited, and liver biopsy remains the gold standard for diagnosis despite its invasive nature and associated risks [7–9].

Current treatment strategies for liver fibrosis primarily focus on lifestyle modifications, such as weight loss and dietary changes, which can effectively halt or reverse fibrosis in some patients [10, 11]. However, adherence to these lifestyle interventions is often poor, necessitating the development of pharmacological approaches. Although anti-fibrotic drugs have shown potential in preclinical studies, there is still a need for effective and safe therapies that can be translated into clinical practice [12–14].

Curcumin’s multi-faceted therapeutic properties make it a promising candidate for liver fibrosis treatment [15]. Studies have demonstrated its ability to modulate various molecular pathways involved in inflammation, oxidative stress, and fibrogenesis [16–18]. However, the clinical translation of curcumin has been limited by its pharmacokinetic challenges. Nanotechnology-based approaches offer a potential solution by enhancing curcumin’s bioavailability and improving its targeted delivery to the liver [19, 20].

Emerging research highlights the potential of curcumin, a polyphenolic compound derived from turmeric, in managing various health conditions. Its therapeutic effects are primarily attributed to its anti-inflammatory, antioxidant, and anti-fibrotic properties. However, curcumin’s clinical application is hindered by its poor bioavailability, rapid metabolism, and low solubility in bodily fluids [21–23]. To overcome these limitations, nanotechnology has been employed to develop Nanocurcumin formulations, which enhance curcumin’s stability, solubility, and bioavailability. Nano carriers such as liposomes, polymer micelles, and solid lipid nanoparticles have shown promise in improving the delivery and efficacy of curcumin in various therapeutic contexts [19, 20].

This study aims to bridge the gap in clinical evidence regarding the efficacy of Nano curcumin in treating liver fibrosis of NAFLD origin. By conducting a randomized controlled trial, we aim to generate data on the therapeutic potential of Nanocurcumin. This evidence will help inform clinical practice and guide the development of effective treatment strategies for liver fibrosis. The primary objective of this study is to evaluate the efficacy of Nanocurcumin supplementation in the treatment and slowing of liver fibrosis and steatosis progression in patients with NAFLD-related fibrosis. Secondary objectives include assessing changes in inflammatory markers, metabolic parameters, liver function tests, anthropometric measures, and blood pressure. The findings from this study will contribute to a better understanding of Nanocurcumin’s role in managing liver fibrosis and may support its potential as a therapeutic option for patients with NAFLD-related fibrosis.

## Methods

### Trial design

This study is a parallel, randomized, double-blind, placebo-controlled trial (IRCT20210427051098N2), which was approved by the institutional review board of the Shahid Sadoughi University of Medical Sciences (SSUMS, Yazd, Iran) and research ethics committee (approval ID: IR. SSU. SPH.REC. 1401. 157) on January 29, 2023. This protocol has been written according to the SPIRIT2013 (Standard Protocol Items: Recommendations for Interventional Trials) checklist (Supplementary) [24].

### Setting

This study is conducted at the Gastroenterology and Liver Clinic of Shariati Hospital affiliated with Tehran University of Medical Sciences (Tehran, Iran). It should be noted that this clinic serves as a major referral center for liver diseases within the region.

### Eligibility criteria

Participants are adults aged 30 to 70 years are included in the study according to the following criteria (Table 1). Participants will be studied after obtaining the written informed consent in Farsi language (Supplementary) by the principle investigator of the study.

**Table 1 Tab1:** Participants eligibility criteria

**Inclusion criteria**: • Stage of Liver Fibrosis: Individuals with liver fibrosis stage ≥ F2. • Diagnosis: Liver fibrosis patients with the origin of non-alcoholic fatty liver disease (NAFLD) and referred to the Gastroenterology Clinic of the Shariati Hospital affiliated with TUMS (Tehran, Iran). **Exclusion Criteria**: • Substance use: Individuals with a history of alcohol addiction, current use of alcohol, or substance abuse problems. • Other liver diseases: Patients with other chronic or acute liver conditions, such as hepatitis B, hepatitis C, biliary diseases, autoimmune liver diseases, or genetic disorders affecting liver metabolism (e.g., hemochromatosis or Wilson’s disease). • Pregnancy and lactation: Women who are pregnant or breastfeeding. • Medication use: Individuals taking hepatotoxic drugs or undergoing treatment with anti-inflammatory drugs, corticosteroids, or hormones. • Serious comorbid conditions: Individuals with severe lung or kidney disease, or active cancer. • Dietary and medication changes: Patients who are on weight loss diets, have recently changed their medication regimen, or are using supplements that could interfere with the study. • Warfarin therapy: Individuals undergoing warfarin therapy due to the increased risk of bleeding and the potential for interaction with Nanocurcumin. • Participation willingness: Those unwilling to participate or adhere to the study protocol. • Side effects of Nanocurcumin supplement: Patients who experience gastrointestinal complications after taking nanocurcumin.	

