### Intervention and control group

In this study, patients in the intervention group receive one capsule of Nanocurcumin supplement (40 mg, twice a day), while patients in the placebo group receive one placebo capsules twice a day. These placebo capsules are designed to be similar to the Nanocurcumin capsules in terms of appearance, color, and smell. Both the Nanocurcumin and placebo capsules are prepared by Exir Nano Sina (ENS) Company in Iran, using Maltodextrin in the placebo capsules. Sufficient quantities of capsule-containing bottles are delivered to patients at the beginning of the study and at the end of weeks 4, 8, 12, and 16. It is recommended that patients consume the capsules with a main meal and cold water. Nausea, Vomiting and Diarrhea are the common side effects of Curcumin when used as powder. However, incidence of these conditions using nanomicellar Curcumin is significantly decreased. Additionally, dietary and physical activity recommendations are provided to the patients in both groups.

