#### Additional outcomes

##### Adherence and tolerability

These are monitored through patient diaries where capsule intake and any adverse effects are recorded daily. If any participant experiences symptoms or other intolerances during the study, they will have the option to withdraw from the intervention. Compliance will be further verified during biweekly telephone check-ins and by counting returned capsules at monthly visits.

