**Assessments**				
Baseline measurements	X			X
Primary outcome	X			X
Secondary outcomes	X			X
Additional outcomes	X			X

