### Data collection

Data will be collected at specified times throughout the study, namely at baseline and at the end of the study. The research staff will be receiving training on correct data collection, entry, and management techniques to ensure data accuracy and reliability.

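### Table 1 makes gastrointestinal complications after taking nanocurcumin an exclusion criterion: as worded, a post-randomisation exclusion that depends on treatment and conflicts with the protocol's own handling of intolerance

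*Protocol article*

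**What the plan says.** The last exclusion criterion in Table 1 (Eligibility criteria), under a label that refers to side effects of the supplement, reads: "Patients who experience gastrointestinal complications after taking nanocurcumin".

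Four other parts of the article bear on it:

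- **Intervention and control group.** Nanocurcumin goes to the intervention arm. In the other arm, "patients in the placebo group receive one placebo capsules twice a day", and those capsules contain maltodextrin.
- **Participant timeline, Table 2.** Eligibility screening is marked at enrolment. Supplementation is marked only in the post-allocation period. No run-in is described.
- **Adherence and tolerability.** Adverse effects are written daily in patient diaries. Participants with symptoms or intolerance are told that "they will have the option to withdraw from the intervention". This covers both arms and concerns the capsules, not the study.
- **Assessment of liver fibrosis and steatosis.** FibroScan is planned for all patients at the start and the end.

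Under Randomization and blinding, a third party labels the containers A or B so that the researchers do not know the assignment.

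**The concern.** An eligibility criterion should be decidable before randomisation. This one refers to an event that, within this trial, can happen only after treatment has begun and, read literally, only in one arm. Removing randomised patients because of something the treatment may have caused means that the patients left in the two arms are no longer comparable by design.

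Three things are at stake:

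- the randomised comparison of liver stiffness and steatosis, if excluded patients are left out of it;
- the account of tolerability, which the protocol lists as an outcome, if their events are left out of the summary;
- the blind, because a rule naming nanocurcumin cannot be applied literally without knowing who takes it.

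The protocol also gives two answers for the same patient: excluded under Table 1, but merely free to stop capsules under Adherence and tolerability.

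**Working it through.** **1. When and to whom the rule applies.** The trigger is a complication after nanocurcumin. Nanocurcumin is given only in the intervention arm and only after allocation, and no earlier exposure is described. The literal rule is therefore post-randomisation and specific to one arm. A placebo patient with the same nausea or diarrhoea does not meet it.

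**2. Can it be applied as written?** Staff see only A or B. They can unblind, extend the rule to any capsule-related gastrointestinal complaint in either arm, or not apply it. The text does not choose. If it is extended to both arms, exclusion still depends on an event that treatment can cause, so the arms may lose different numbers and kinds of patient.

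**3. The planned sample size, as reference.** Inputs from Sample size: effect 0.9, type I error 5% (two-sided assumed), power 80%, attrition 10%.

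- t-test: 20.39, rounded up to 21 per arm; 21/0.90 = 23.3, rounded up to 24; total 48.
- Mann-Whitney: 20.39/0.955 = 21.35, rounded up to 22; 22/0.90 = 24.4, rounded up to 25; total 50.

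The stated 50 is reproduced. The sample size is not at fault.

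**4. Cost in power** (two-sided t-test, effect 0.9, 25 randomised per arm). The exclusion fractions are assumptions, because the article gives no gastrointestinal event rate.

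| Active arm excluded | Power, with 10% other loss in both arms |
|---|---|
| 0% | 0.839 |
| 10% | 0.818 |
| 20% | 0.792 |

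The loss is modest.

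**5. Possible bias.** Let g be the fraction of the active arm excluded, and s the difference in mean outcome between excluded and retained patients, in SD. The full-arm mean is (1 − g) × m + g × (m + s) = m + g × s, where m is the mean of those retained. Leaving out the excluded patients shifts the arm mean by g × s in absolute size.

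| g | s = 0.3 | s = 0.5 | s = 1.0 |
|---|---|---|---|
| 10% | 0.03 | 0.05 | 0.10 |
| 20% | 0.06 | 0.10 | 0.20 |

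Relative to the planned effect, 0.03/0.9 = 3% and 0.20/0.9 = 22%. In an arm of 25, 20% is five patients. Both g and s are assumptions, and the sign of s is unknown. If the rule were applied to both arms, the bias would be the difference between the two arms' g × s terms, which may be smaller.

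**The case against.** The strongest reply is that the line is only clumsy. Table 2 puts eligibility screening before allocation, and the other Table 1 items describe patients at entry, so this one may mean intolerance already known. That reading cannot be excluded, but it is strained: the item is headed as a side effect of the study supplement, and no earlier exposure is described. If it is what was meant, the wording still has to change.

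Second, nothing says that excluded patients leave the analysis. The article names no analysis population, which an article may properly leave to a fuller document. The end-of-study scan in all patients, and withdrawal from the intervention rather than the study, point towards keeping them. This stands: the rule can bias the comparison, but the documents do not show that it will.

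A reader might also infer more than the text supports:

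- **That only active-arm patients could be removed.** This is true of the wording. Blinded staff could not apply it that way.
- **That the active-arm gastrointestinal rate would be 0% by construction.** Diaries record adverse effects daily, so an event would normally be on record before any exclusion. No passage plans to discard it.
- **That the bias always favours nanocurcumin.** This requires intolerant patients to have worse liver outcomes. The documents do not link the two.
- **That the criterion "Those unwilling to participate or adhere to the study protocol" is a second post-randomisation exclusion.** It reads as willingness at entry.
- **That the schedule loses the tolerability data.** Table 2 marks additional outcomes at enrolment and close-out, and Data collection gives the times as "namely at baseline and at the end of the study". But Adherence and tolerability expressly sets daily diaries, biweekly calls and monthly capsule counts. Any mismatch there is a separate matter of presentation.

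**Conclusion.** The point holds in a limited form. Table 1 states an exclusion that, as worded, operates after randomisation, depends on treatment and names one arm's product. It contradicts the section on adherence and tolerability and does not fit the plan to scan all patients at the end. This is a stated rule, not a missing detail.

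The harm is conditional: it arises only if patients excluded under the rule leave the analysis or the adverse-event summary. The bias could then be from 3% to 22% of the planned effect under the assumed ranges, in either direction, and active-arm gastrointestinal events could be under-reported. The main risk is selection rather than lost power. The documents give no event rate and no outcome difference for intolerant patients, so these figures show scale and are not estimates.

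**What to change.** Reconcile Table 1 with Adherence and tolerability:

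1. Delete the line, or restrict it to intolerance known before consent.
2. State that gastrointestinal events in both arms are recorded and reported.
3. State that all randomised patients, including those who stop capsules, have the planned end-of-study assessments and are analysed in their allocated group.

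Decisions about stopping capsules are not changed by this.

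The cost is a short wording change, and the end-of-study visit is already planned. The downside is some dilution of the effect estimate by patients who stopped. The article expected recruitment to end by the close of 2024 and the trial by mid-2025, and it appeared in February 2026, so follow-up may already be over. In that case, apply points 2 and 3 to the analysis and reporting: report by arm how many patients, if any, were excluded under this line, and include their available outcome data and diary-recorded events.
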